### **8.3 Study procedures**

#### **8.3.1 Baseline screening**

Subjects who sign informed consent will be eligible for participation. The treating physician, if need be in collaboration with study staff, will confirm the patient meets the in- and exclusion criteria. Namely, screening will include evaluation of SARS-CoV-2 PCR results, vital signs, concomitant medication and known allergies.

#### **8.3.2 Study medication**

Trial medication will be delivered by the local pharmacy coded only with the trial identifier and the patient study code (see also section 6.8). Directly after inclusion (defined as study day 1) in the study patients will take either 3 tablets containing 333mcg K2 each (for a total dose of 1000mcg) or 3 matched placebo tablets. Patients will continue taking either 1000mcg Vitamin K2 MK-7 once a day or matched placebo for up to 14 days. Treatment will be discontinued at discharge.

#### **8.3.3 Follow-up of adverse events**

Adverse events will be monitored until discontinuation of treatment, at 28 days post inclusion mortality will be assessed.

When recording adverse events special attention will be paid to progression of respiratory insufficiency, thrombotic events, pulmonary embolism or deep venous thrombosis and bleeding. Toxicities will be scored according to the most recent version of the NCI Common Terminology Criteria for Adverse Events (CTCAE) version 5 (see Appendix).

The treating physician will determine whether adverse events require additional testing, such as, for example, pulmonary CT angiography in the case of suspected pulmonary embolism or coagulation parameters in the case of bleeding.

#### **8.3.4 Vital signs**

Vital signs including body temperature, respiration rate, oxygen saturation measured by pulse oximetry, blood pressure and pulse measurements will be determined and recorded daily as part of routine clinical practice at least once a day.

Systolic and diastolic blood pressure will be measured while the subject is lying down or sitting with back supported, using an automated validated device, with an appropriately sized cuff. In case the cuff sizes available are not large enough for the subject's arm circumference, a sphygmomanometer with an appropriately sized cuff may be used.

Temperature will be measured according to local practice, consistently throughout the study. The thermometer used should have a precision of 0.1°C. The same route should be used throughout the study.

If vital signs are out-of-range, the treating nurse or physician may obtain additional readings at their discretion.

### **8.3.5 Clinical laboratory measurements**

At baseline (within 24 hours of admission) and subsequently three times per week, the following laboratory tests are performed: full blood count, electrolytes (sodium, potassium, calcium), creatinine, liver enzymes (bilirubin, ALAT, ASAT and LDH), c-reactive protein (CRP) and albumin. D-dimer will be performed at all follow-up time points (though not at baseline).

Arterial blood gas can be performed at the discretion of the treating physician but will not be part of routine measurements.

Performing additional laboratory analyses such as urinalysis, d-dimer, or cardiac enzymes in the context of standard patient care is at the discretion of the treating physician.

### **8.3.6 Dp-ucMGP**

At baseline (within 24 hours of inclusion) and subsequently three times per week, EDTA plasma will be frozen at -80 degrees Celsius for retrospective determination of dp-ucMGP. Circulating dp-ucMGP levels will be determined using the commercially available IVD CE marked chemiluminescent InaKif MGP assay on the IDS-iSYS system (IDS, Boldon, UK). 50 µL of patient sample or calibrators are incubated with magnetic particles coated with murine monoclonal dpMGP antibody, an acridinium labelled murine monoclonal ucMGP antibody and assay buffer. The magnetic particles are captured using a magnet and a wash step performed to remove any unbound analyte. Trigger reagents are added, the resulting light emitted by the acridinium label is directly proportional to the concentration of dp-ucMGP in the sample. The within-run and total precision of this assay is 0.8 – 6.2% and 3.0 – 8.2%, respectively. The assay measuring range is between 300 – 12,000 pmol/L and was previously found to be linear up to 11,651 pmol/L. Dp-ucMGP values below 500 pmol/L are considered to be in the normal healthy range.

### **8.3.7 PIVKA-II**

At baseline (within 24 hours of inclusion) and subsequently three times per week, EDTA plasma will be frozen at -80 degrees Celsius for retrospective determination of dp-ucMGP. Plasma PIVKA-II concentrations will be measured with ELISA using a commercially available kit from Roche Diagnostics (Elecsys® PIVKA-II).

### **8.3.8 Desmosine**

The rate of elastin degradation will be quantified by measuring plasma (p)DES levels. At baseline (within 24 hours of inclusion) and subsequently three times per week, EDTA plasma

will be frozen at -80 degrees Celsius for retrospective determination of pDES. Subjects with the highest pDES are assumed to have the highest rates of elastin degradation. Isodesmosine and desmosine fractions will be measured separately by liquid chromatography-tandem mass spectrometry as previously described using deuterium-labelled desmosine as internal standard [57, 58].

### **8.3.9 Exploratory laboratory measurements**

At every time point extra EDTA plasma, citrate plasma and serum will be aliquotted and frozen at -80 degrees Celsius for retrospective analysis of exploratory outcomes. These can include measurements related to protein S and coagulation activity, including levels of (undercarboxylated) protein S, normative APC sensitivity ratio and prothrombin (Echis Carinato test), TFPI concentration and vitamin D levels.

Levels of circulating active MGP can be measured by ELISA. Furthermore, levels of inflammatory markers parameters including CRP, d-dimer, ferritin, IL-6, TNF- $\alpha$ , IFN- $\gamma$  and s-IL-2r can be measured by ELISA or Multiplex assay.

VKORC1 polymorphism can be determined as follows. High Pure PCR Template Preparation Kit (Roche Diagnostics, Mannheim, Germany) will be used for isolation of DNA, according to the manufacturer's instructions. For genotyping the C1173T (rs 9934438) and G-1639A (rs 9923231) single nucleotide polymorphisms of the VKORC1 gene, real-time PCR Fluorescence Resonance Energy Transfer (FRET) analyses will be performed. FRET LightMix® assays (cat.-no 40-0302-16, TIB MOLBIOL, Berlin, Germany) on the LightCycler® (Roche Diagnostics) will be used, according to the manufacturer's protocols. The assay consists of a duplex reaction measuring the melting curves of the used specific fluorescent probes in two different channels, each with a distinct wavelength. With each run positive (heterozygote, provided with the kit) and negative controls will be determined.

### **8.3.10 Chest Computer Tomography (CT) scans**

Computed tomography (CT) is performed at baseline and on day 5 after study start for assessing pulmonary involvement score (Dofferhoff *et al.* CID 2020)). If patients are discharged before day 5 the second CT scan is made prior to discharge. Severity of COVID-19 pneumonia will be quantified and expressed as volume percentage of lung involvement on low dose chest CT by a specialized chest radiologist at University Medical Center Utrecht (UMCU) as described below.

Thin slice CT scans are acquired by using a Philips Ingenuity multi-detector row scanner (Philips Healthcare). CT images of 1-mm thickness are reconstructed by using iterative model-based reconstruction in the axial plane.

Quantitative measurements of the volume of ground glass and consolidation will be undertaken using the Intellispace Portal (COPD package, Intellispace version 10, Philips Healthcare). In the software, first the lungs are segmented from the chest wall and major vessels and main bronchi. Manual adjustments are implemented where required by a board-certified chest radiologist. Subsequently, the lung voxels are counted to derive a total lung volume in milliliters. Diseased lung tissue is defined as those voxels with an attenuation of Hounsfield Units (HU) > -700. The abnormal voxels are expressed as a percentage diseased lung of the total volume. HU value at the 85th percentile will be used.

#### **8.3.11 Vitamin K epoxide reductase complex subunit 1 (VKORC-1) gene polymorphisms**

At one time point during the trial we will take a DNA mouth swab from each patient for determination of the single-nucleotide polymorphism (SNP) C1173T on the VKORC1 gene, using the Roche Diagnostics LightCycler® (Roche Applied Science, Indianapolis, IN) diagnostic test.

### 8.3.12 Study flow chart

|                                                                      | Inclusion      | Hospital admission |                    | Follow-up |
|----------------------------------------------------------------------|----------------|--------------------|--------------------|-----------|
| Study day                                                            | 1              | 2-14   | 15-27  | 28        |
| Eligibility criteria + informed consent                              | X              |                    |                    |           |
| Collection of demographic data and medical history                   | X              |                    |                    |           |
| Physical examination and vital signs                     | X              | X                  | X                  |           |
| Vitamin K2 MK-7 or placebo treatment                                 | X              | X                  |                    |           |
| Collecting (serious) adverse events                                  |                | as necessary       |                    |           |
| Collecting adverse events                                            |                | X                  |                    | X         |
| Laboratory testing                                     | X  | X                  | X                  |           |
| dp-ucMGP, PIVKA-II, desmosine                          | X  | X                  | X                  |           |
| Plasma and serum collection for exploratory endpoints  | X  | X                  | X                  |           |
| CT scan                                                              | X  | X      |                    |           |

 Vital signs are collected at least 3 times per day until discharge, physical examination is performed as necessary

 Blood is collected three times per week while the patient is admitted to the hospital

 Full blood count, electrolytes (sodium, potassium, calcium), creatinine, liver enzymes (bilirubin, ALAT, ASAT and LDH), c-reactive protein (CRP) and albumin; d-dimer will be determined at all follow-up time points (though not at baseline)

 Analysis performed retrospectively

 Performed at baseline and on day 5, if patient is discharged before day 5 a CT scan is performed prior to discharge, if the CT scan cannot be made on day 5 it is made up to a maximum of 24 hours after day 5

 Number of study days dependent on discharge

 Or in the previous 24 hours

 Or in the previous 52 hours

#### **8.4 Withdrawal of individual subjects**

Subjects can leave the study at any time for any reason if they wish to do so without any consequences. The investigator can decide to withdraw a subject from the study for urgent medical reasons or the following reasons:

- Refusal of patient to continue protocol treatment
- No compliance of the patient: patient is unable or unwilling to adhere to the treatment schedule and/or procedures required by the protocol

Patients who are withdrawn from protocol treatment will receive medical care according to local hospital practice.

If a patient states that he or she withdraws their consent to participate in the trial, the investigator should attempt to verify the patient's intent and their reason for withdrawal, and record this in the patient's medical file.

The patient can refuse further treatment and/or procedures according to protocol, while still consenting with further follow up data collection. The patient can refuse further treatment and/or procedures according to protocol and withdraw consent for further follow up data collection.

For patients who are lost to follow-up (i.e. those subjects whose status at 28 days post treatment is unclear because they cannot be contacted without having stated an intention to withdraw), extensive effort (i.e. documented phone calls and e-mails) will be undertaken to determine his or her health status. The investigator should show "due diligence" by documenting in the source documents steps taken to contact the patient.

##### **8.4.1 Specific criteria for withdrawal**

Patients should be withdrawn from protocol treatment if any of the following criteria for withdrawal are met:

- Patient is not eligible to participate in the study in hindsight
- The occurrence of an adverse event preventing further treatment Patient becomes dialysis-dependent

#### **8.5 Replacement of individual subjects after withdrawal**

If a patient withdraws or is withdrawn before he or she has received the first treatment (vitamin K2 or placebo), he/she will be replaced with another suitable patient.

### **8.6 Follow-up of subjects withdrawn from treatment**

After discharge the investigator will follow-up the patients status as alive or deceased after 28 days after study intervention. If the patient is seen in outpatient clinic by a treating physician this information may be gathered from the patient's medical file. Alternatively, an investigator can call the patient's primary care physician or the patient at home to ascertain this information.

### **8.7 Premature termination of the study**

The sponsor may decide to terminate the study prematurely based on the following criteria:

- There is evidence of an unacceptable risk for study patients (i.e. safety issue);
- There is reason to conclude that continuation of the study cannot serve a scientific purpose following confirmation of the SMC; or
- The SMC recommends to end the trial based on viable arguments other than described above.

The sponsor will promptly notify all concerned investigators, the Ethics Committee(s) and the regulatory authorities of the decision to terminate the study. The sponsor will provide information regarding the time lines of study termination and instructions regarding treatment and data collection of enrolled patients.

## 9. SAFETY REPORTING

### 9.1 Temporary halt for reasons of subject safety

In accordance with section 10, subsection 4, of the WMO, the sponsor will suspend the study if there is sufficient ground that continuation of the study will jeopardise subject health or safety. The sponsor will notify the accredited METC without undue delay of a temporary halt including the reason for such an action. The study will be suspended pending a further positive decision by the accredited METC. The investigator will take care that all subjects are kept informed.

### 9.2 AEs and SAEs

#### 9.2.1 Adverse events (AEs)

Adverse events are defined as any undesirable experience occurring to a subject during the study, whether or not considered related to the experimental intervention. All adverse events reported spontaneously by the subject or observed by the treating physician, the investigator or the research nurses are recorded into the patient's medical files.

Given the expected large number of adverse events occurring in patients admitted with COVID-19, only grade 3 and 4 adverse events will be reported in the Electronic Case Report Forms (eCRFs). Grade 3 and 4 adverse events will be recorded if they begin or become more severe between the time of the first treatment and discontinuation of treatment.

The severity of any adverse events, including any lab abnormality, will be determined by using the Common Terminology Criteria for Adverse Events, version 5 (NCI CTAE, appendix 1). The criteria are also available online at <http://ctep.cancer.gov>.

In any case where the NCI CTCAE criteria do not apply, severity should be defined according to the following criteria:

**Mild (grade 1):** awareness of symptoms that are easily tolerated and do not interfere with usual daily activity

**Moderate (grade 2):** discomfort that interferes with or limits usual daily activity

**Severe (grade 3):** disabling, with subsequent inability to perform usual daily activity, resulting in absence or required bed rest

**Life threatening (grade 4):** immediate risk of death from the reaction as it occurred

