#### **9.4 Follow-up of (serious) adverse events**

##### **9.4.1 (Serious) adverse event data collection**

Safety assessments will be performed and recorded by the investigators. All adverse events/reactions (solicited and unsolicited), noted by the investigators will be accurately documented in the case report form by the investigators. For each event/reaction the following details will be recorded:

1. Description of the event(s)/reaction(s)
2. Date and time of occurrence
3. Duration
4. Intensity
5. Relationship with the intervention
6. Action taken, including treatment
7. Outcome

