### **9.5 Safety Monitoring Committee**

An independent Safety Monitoring Committee (SMC) will be appointed, including 3 individuals. Their main responsibility will be an interim analysis of all serious adverse events and occurred thromboembolisms, making the decision to halting further study procedures. A safety report including a list of all reported serious adverse events and thromboembolisms will be prepared for review by the SMC after the first 20 patients have completed follow-up and at the end of the study.

The advice(s) of the SMC will be sent to the sponsor of the study. Should the sponsor decide not to fully implement the advice of the SMC, the sponsor will send the advice to the METC that assessed the study, including a note to substantiate why (part of) the advice of the SMC will not be followed.

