#### **9.5.1 Review of safety data by the safety monitor and SMC**

A safety report including information on all reported serious adverse events and thromboembolisms will be compiled after the twentieth patient has reached the fourteenth day of the study (discontinuation of treatment) and at the end of the study. These reports will be prepared in a blinded manner by a clinical investigator and sent to the SMC and all principle investigators. During a closed session, the SMC will be able to de-blind the information prior to their review.

The responsibilities of the SMC are described in the SMC Charter. In short, the SMC will evaluate the number and nature of any SAEs and thromboembolisms that occurred during the study. In the case of statistically significant increase in the number of SAEs and thromboembolisms in the intervention group, compared to the control group, the SMC will advise the sponsor to halt the study pending further review.

The advice(s) of the SMC will only be communicated to the METC when the sponsor does not follow this. With this notification a statement will be included indicating whether the advice will be followed.

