### **10.3 Interim analysis**

There will be no interim data analysis. Fifty percent of the study patients, 10 intervention and 10 controls, has insufficient power to conduct a classical interim analysis to evaluate either the primary or secondary endpoints. Instead, the SMC will conduct a safety analysis that will focus on identifying any serious negative effect of the study intervention on patient safety.

The SMC will have access to the unblinded patient data for all serious adverse events and thromboembolisms that occurred during the trial. If a significantly higher number of SAEs or thromboembolisms occurred in the intervention group compared to the control group, the SMC will advise the sponsor to place the study on hold pending a more extensive review. In the case of such a safety hold, the trial will only be restarted after discussion with the METC that assessed the study.

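### Sections 9.2.1 and 9.4.1 conflict on which adverse events enter the eCRF, so a thromboembolism below grade 3 has no assured eCRF route to the SMC's count

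*Protocol*

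**What the plan says.** Protocol 9.2.1 sets two levels of recording. At source, "All adverse events reported spontaneously by the subject or observed by the treating physician, the investigator or the research nurses are recorded" in the medical file, whatever the grade. For the trial database the rule is narrower: "only grade 3 and 4 adverse events will be reported in the Electronic Case Report Forms (eCRFs"). The reason given is the large number of events expected in patients admitted with COVID-19. No event class is exempt.

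Protocol 9.4.1 gives a different rule for the same form: "All adverse events/reactions (solicited and unsolicited), noted by the investigators will be accurately documented in the case report form by the investigators". It has no grade limit and does not refer back to 9.2.1.

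Thromboembolism is then treated as a safety item in its own right:

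- 8.3.3: when events are recorded, "special attention will be paid to progression of respiratory insufficiency, thrombotic events, pulmonary embolism or deep venous thrombosis and bleeding".
- 9.5: "A safety report including a list of all reported serious adverse events and thromboembolisms will be prepared for review by the SMC".
- 9.5.1: "the SMC will evaluate the number and nature of any SAEs and thromboembolisms that occurred during the study".
- 10.3: the trigger for advising a hold is "If a significantly higher number of SAEs or thromboembolisms occurred in the intervention group compared to the control group".

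None of these four places sets a grade limit. None names the data source for the SMC's list.

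**The concern.** The two recording rules cannot both be followed. A site that works to 9.2.1 leaves a thromboembolism below grade 3 out of the eCRF; a site that works to 9.4.1 enters it. The protocol does not say which section prevails. A later analysis plan cannot settle it either, because an event that was never entered is not there to analyse.

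The conflict bears on the one event class, apart from SAEs, on which the SMC is asked to act. If the person preparing the SMC report works from the eCRF as 9.2.1 defines it, lower-grade thromboembolisms will be absent from a list that is meant to have no grade limit. With 10 patients per arm at the interim safety review and 20 per arm at the end, the comparison rests on very few events, so one or two missing events matter. The SMC count and the count in the final report could also differ if they are drawn from different records.

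**Working it through.** **Step 1. The rules side by side**

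| Section | Record | Grade limit |
|---|---|---|
| 9.2.1 | Medical file | None |
| 9.2.1 | eCRF | Grade 3 and 4 only |
| 9.4.1 | Case report form | None |
| 9.5, 9.5.1, 10.3 | SMC list, evaluation and hold trigger | None for thromboembolism |
| 12.4 | Trial master file (SAE and thromboembolism data) | None |

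Rows two and three contradict each other: 12.2 makes the case report form electronic, so they concern the same form. Row four needs data that row two does not supply.

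**Step 2. Other routes by which a lower-grade thromboembolism could reach the SMC**

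- *Medical file.* The event is there, but no section assigns anyone to extract thromboembolisms from the files for the SMC.
- *Trial master file.* 12.4 is a retention rule. It gives no form, responsible person or timing for collection.
- *SAE reporting.* 9.2.2 counts an event that prolongs the stay as serious only if the investigator judges it to lie outside the natural course of COVID-19. 13.2 describes thrombotic complications as frequent within that normal course. Read together, these allow a thrombosis to be judged non-serious on that criterion. The important-medical-event criterion remains open, at the investigator's judgement.
- *Monitoring.* 12.6 has SAE documentation fully verified, but checks the recording of primary and safety variables in only 10% of subjects (4).

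Each route may deliver the event. None is stated to do so.

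**Step 3. How sensitive the comparison is to one event**

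The protocol has no figure of its own to reproduce here. 10.3 gives 10 patients per arm at the interim review; 8.2 gives 20 per arm in total. 10.2 names the chi-square or Fisher's exact test for complications, but neither the test nor the alpha for the SMC is given. I assume a two-sided Fisher's exact test at 0.05.

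With n per arm, k intervention events and no control events, p = 2 × C(n, k) / C(2n, k).

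- n = 10, k = 5: 2 × 252 / 15,504 = 0.033
- n = 10, k = 4: 2 × 210 / 4,845 = 0.087
- n = 20, k = 5: 2 × 15,504 / 658,008 = 0.047
- n = 20, k = 4: 2 × 4,845 / 91,390 = 0.106

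At either size, losing one of five events moves the result across 0.05.

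**Step 4. Loss of a fraction of events (assumed rates)**

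The protocol gives no thromboembolism rate and no grade split. Purely for illustration, take true rates of 40% and 10%, with the same fraction unrecorded in both arms. The recorded rates are then 40% and 10%, 30% and 7.5%, or 20% and 5%. The chance of a significant excess in the intervention arm is:

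| Unrecorded | 10 per arm | 20 per arm |
|---|---|---|
| 0% | 15% | 49% |
| 25% | 7% | 33% |
| 50% | 2% | 17% |

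Power at the interim is low even with full capture. Incomplete capture lowers it further.

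**The case against.** The strongest reply is that no undercount has been shown, and that stands. A reader might infer from 9.2.1 that the SMC's thromboembolism count will be too low. The protocol does not support that: it never says the SMC list comes from the eCRF, all events are in the medical files, 12.4 gives thromboembolism data a place outside the grade rule, some lower-grade events may qualify as SAEs, and the SMC Charter is not at hand.

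Four further inferences are tempting and should be resisted.

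- *That a non-disabling thrombosis is grade 2 by the protocol's own wording.* The severity descriptions in 9.2.1 apply only where CTCAE does not. CTCAE version 5 governs, and its appendix is not shown, so the number of thromboembolisms below grade 3 cannot be derived.
- *That thromboembolism is rare, so the stated reason for the grade limit cannot apply to it.* 7.3 and 13.2 describe these complications as frequent. The case for an exemption is that this is one named class on which the SMC acts.
- *That the secondary safety endpoint loses events.* It is defined as grade 3 and 4 events in 8.1.2, so it is complete by its own definition.
- *That bleeding has the same gap.* Bleeding is listed for special attention in 8.3.3, but it is not a separate SMC item and reaches the committee only as an SAE.

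What these replies do not remove is the contradiction between 9.2.1 and 9.4.1, or the lack of a stated path from a lower-grade thromboembolism to the SMC report.

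**Conclusion.** The point holds as a contradiction with a safety consequence that is possible but not demonstrated. Sections 9.2.1 and 9.4.1 give incompatible eCRF rules, and under 9.2.1 the SMC's comparison of thromboembolisms at any grade has no eCRF source below grade 3. How many events are affected cannot be derived from the protocol; it could be none. The sensitivity is clear under the assumed test: one event separates p = 0.033 from p = 0.087 at 10 per arm, and p = 0.047 from p = 0.106 at 20 per arm. The table of assumed rates shows direction only and is not a forecast. The protocol should be amended on this point, since the change is small and protects the safety review. The primary analyses and the grade 3–4 endpoint are unaffected.

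**What to change.** - In 9.2.1, keep the grade 3 and 4 limit for adverse events in general and add one exception: every thromboembolic event is entered in the eCRF whatever its grade.
- Reword 9.4.1 so that it refers to the rule in 9.2.1 instead of requiring all events in the form.
- In 9.5.1, state that the SMC report and the final between-arm count of thromboembolisms are both drawn from these eCRF records, so that the two agree.

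Recording bleeding at any grade is optional; 8.3.3 would support it, but the SMC gap does not require it. The secondary endpoint in 8.1.2 needs no change.

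The cost is a sentence or two in three sections, an eCRF instruction, and a small amount of extra data entry for lower-grade thromboembolisms.
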